Statistical analyses will take into account the intention-to-treat analysis. Missing data will be handled using last observation carried forward (LOCF) imputation technique. Arithmetic means and standard deviation will be used for the general characteristics of the study population. Univariate statistical tests will be performed to compare the experimental group and control group at the baseline. A generalized linear model, linear regression, will be considered to study the independent effect of OMT on primary endpoint and secondary endpoints, taking into account all possible confounders. The significance level will be at α=0.01. Differences between the groups will be presented as mean with 95% CI or in categories with OR for categorical data.

The statistical program in use for randomization and data analyses is R 18.

Sample size

Sample size calculation used an effect size of 0.3 calculated from previous studies, considering a mean difference of 4 days between experimental and control group and a SD of 14. The statistical power is set at 0.90 and an alfa level equal to 0.01. This produces a sample size of 333 per group. To prevent loss of power, the sample size is increased up to 345 subjects per group. The whole sample (N=690) is then divided, with a final result of N=230 preterm infants for each NICU. A longer period of study enrollment has been considered a strategy to achieve the estimated sample size.

Coordinating center

The coordinating center EBOM consists of an executive division, President and Vice-President, an administration office, a group of researchers, an information technology consultant and a senior biostatistician.

The coordinating center collaborates with the A.I.O.T. - Accademia Italiana Osteopatia Tradizionale.

ETHICS AND DISSEMINATION

During the routine initial post-delivery consultation, the neonatologist approaches parents or legal guardians explaining the patient information sheet. Written informed consent will be then obtained from the above-mentioned guardians at study enrollment. Participation is voluntary and data collected will be sent to the coordinating centre using an anonymous identification for each patient.

The trail is approved by the ethical committee of Macerata hospital (n°22/int./CEI/27239) and it is under review by the other regional ethics committees. Moreover the trial has been registered on clinicaltrial.gov (identifier NCT01645137).

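### The effect size of 0.3 that yields 333 per group does not equal the printed 4 days over SD 14 (0.286), for which power is about 86 to 88%, not 90%

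*Protocol*

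**What the plan says.** The Sample size section of the protocol gives, in one sentence, a standardised effect and the raw figures offered with it: "effect size of 0.3 calculated from previous studies, considering a mean difference of 4 days between experimental and control group and a SD of 14". It continues: "The statistical power is set at 0.90 and an alfa level equal to 0.01. This produces a sample size of 333 per group". As a guard against lost power, "the sample size is increased up to 345 subjects per group", which makes 690 in total and 230 in each of three units. Allocation is 1:1 (Randomization process).

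The Statistical analyses section uses the same error rate: "The significance level will be at α=0.01". Neither section says whether the test is one-sided or two-sided. The protocol gives no expected rate of loss and no variance reduction from covariates in the sample size calculation.

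**The concern.** A standardised effect is the mean difference divided by the SD. The sentence therefore gives one quantity twice, with two values: 0.3, and 4/14 = 0.286. The required sample size varies with the inverse square of the effect, so a 5% difference in effect becomes a 10% difference in n: (0.3/0.2857)² = 1.1025.

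If n was computed from 0.3, the stated 90% power does not apply to the 4 days and SD 14 that a clinical reader will take as the target. What is at stake is the accuracy of the power statement for the primary outcome, length of stay. The type I error and the validity of the treatment estimate are not affected. The protocol promises reporting according to CONSORT, so the mismatch would probably be carried into the trial report.

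**Working it through.** **Inputs** (protocol, Sample size, except where noted): alpha 0.01; power 0.90; effect size 0.3; difference 4 days; SD 14; 333 per group, raised to 345; allocation 1:1 (Randomization process). Sidedness is not stated, so both versions were run.

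**1. Reproducing 333.** The normal approximation for n per group, two-sided, is

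n = 2 (z₀.₉₉₅ + z₀.₉₀)² / d², with z₀.₉₉₅ = 2.576 and z₀.₉₀ = 1.282.

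The exact two-sample t-test (noncentral t) adds one or two per group.

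| Effect size | Sides | Normal | t-test | Whole number (t-test) |
|---|---|---|---|---|
| 0.30 | two | 330.7 | 332.3 | **333** |
| 4/14 = 0.2857 | two | 364.5 | 366.2 | 367 |
| 0.30 | one | 289.3 | 290.6 | 291 |
| 4/14 = 0.2857 | one | 318.9 | 320.3 | 321 |

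Of these four, only d = 0.30 with a two-sided test returns the protocol's figure, and it does so exactly. The calculation therefore used 0.30, and a two-sided test is the reasonable inference.

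**2. What 4 days and SD 14 need.** With d = 0.2857, two-sided, the t-test needs 366.2, so 367 per group (366 gives 0.8998). This is 34 more than 333 and 22 more than 345. The protocol's addition is 345 − 333 = 12.

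**3. Power at the planned sizes, two-sided alpha 0.01.**

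| Analysed per group | d = 0.30 (t-test) | d = 4/14 (t-test) | d = 4/14 (normal) |
|---|---|---|---|
| 333 | 0.901 | 0.865 | 0.867 |
| 345 | 0.912 | 0.879 | 0.880 |

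For the printed difference and SD, the type II error by the t-test is 13.5% at 333 and 12.1% at 345, against the 10% implied by the protocol.

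**4. Difference detectable with 90% power at SD 14 (t-test).**
- 333 per group: d = 0.2997, and 0.2997 × 14 = 4.20 days.
- 345 per group: d = 0.2944, and 0.2944 × 14 = 4.12 days.

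**5. Covariate adjustment that would restore 90% for 4 days.** If covariates explain a share R² of the variance, the required n falls to about 366.2 × (1 − R²).
- 345 analysed: R² = 1 − 345/366.2 = 0.058, about 0.06.
- 333 analysed: R² = 1 − 333/366.2 = 0.091, between 0.09 and 0.10.

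The protocol gives no R², so these are the values that would have to be assumed, not results.

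**The case against.** The strongest defence is that the protocol names 0.3 as the input and says it came from previous studies. With that input, 333 is correct and 345 gives about 91%. The 4 and the 14 are whole numbers and may be the rounded figures: 4.2/14 and 4.05/13.5 both equal 0.30, and whole-number rounding allows anything from 3.5/14.5 = 0.24 to 4.5/13.5 = 0.33. This stands. A reader might infer that the planners rounded 4/14 up to 0.3, but the document does not show which figure was rounded. If the raw figures were the rounded ones, the printed inputs still fail to give the printed n and need correcting.

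The second defence is size. The detectable difference moves from 4 days to 4.12 or 4.20, which is 0.12 × 24 = 3 hours or 0.20 × 24 = 5 hours. At 345 the loss of power is about 2 points. This also stands, and it rules out the reading that the trial is seriously underpowered or needs more infants. The protocol attaches 90% to 333, however, and there the gap is 3.5 points.

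The claim that no reserve remains for losses holds only if 4/14 is the true target. With d = 0.30, the 12 extra per group are a real margin.

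Finally, it may be said that adjustment for gestational age and birth weight would recover the power. The Introduction does call length of stay strongly associated with both. But the Statistical analyses section says only that regression will be considered, names no covariates and gives no R². Recovery is plausible, but the document does not establish it.

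**Conclusion.** The point holds as an internal inconsistency. The figures in the Sample size section do not agree with one another, and the stated 90% power does not hold for the 4-day difference and SD of 14 printed beside it. For those values power is about 86.5% with 333 analysed per group and 87.9% with 345, and 367 per group would be needed for 90%.

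This rests on a two-sided test, which is inferred. At a one-sided alpha of 0.01, 345 per group would give about 92% for 4/14, but no one-sided calculation gives 333. It also rests on taking 4 and 14 as exact and on an unadjusted comparison of means, which is the comparison that reproduces the protocol's figure.

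The severity is moderate to minor. The power statement is wrong as printed, but the design, the significance level and the analysis are unaffected.

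**What to change.** Keep N = 690. State that the test is two-sided, and make the figures agree in one of three ways:

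- *d = 4/14 = 0.286; at two-sided alpha 0.01, power is about 88% with 345 per group and about 86% with 333 analysable.*
- *90% power for a difference of 4.2 days (SD 14) with 333 per group, two-sided alpha 0.01.*
- Print the unrounded difference and SD from the previous studies, if they do give 0.30.

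The sponsor can choose by checking the original calculation. If the text is to mention a gain from covariate adjustment, it should name the covariates and present the gain as an assumption: R² of about 0.06 with 345 analysed, or between 0.09 and 0.10 with 333. Otherwise it should leave the gain out.

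The cost is wording only, with no change to recruitment, conduct or analysis. Under the first option the stated power becomes slightly less favourable.
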